### Quality of life

The World Health Organization’s Quality of Life-BREF (WHOQOL-BREF) instrument measured quality of life across the four domains of physical health, psychological health, social relationships and environment. This standardised 26-item questionnaire asked participants to rate the degree to which they experienced the items in the past two weeks on a five-point Likert scale (low score of ‘1’ to high score of ‘5’), with a higher score indicating better quality of life. The WHOQOL-BREF has been validated as a reliable brief instrument to assess quality of life in homeless individuals across all four domains [41].

### Substance use

Substance use patterns were measured by a number of variables. Lifetime and three-month use of the following substances was recorded (yes/no): tobacco; alcohol; cannabis; amphetamines; cocaine; inhalants; sedatives; hallucinogens; and opioids. Those participants who reported use in the past three months were asked to indicate their frequency of use (once weekly or less/more than weekly), the frequency they had a strong desire or urge to use each substance (once weekly or less/more than weekly), and the frequency that health, social, legal or financial problems resulted from the use of each substance (once monthly or less/more than monthly). Non-medical use of a drug by injection in lifetime (yes/no) and the past three months (yes/no) was recorded. If participants had injected in the past three months, they were asked to rate their frequency of injecting (once weekly or less/more than weekly).

### Service utilisation

To measure health service utilisation, participants were asked if they had attended the following services over the past 12 months (yes/no): inpatient hospital services for physical health; inpatient hospital services for mental health; emergency department (ED) for physical health; ED for mental health; ambulance call-out; drug and alcohol treatment facility; general practitioner (GP) for physical health; GP for mental health; or a specialist mental health service. From this, the total number of different health services utilised over the past 12 months was computed (range 0–8). Participants were asked to report the number of days they had utilised each health service over the past 12 months (range 0–365 days). For example, ‘*In the past 12 months, how many days in total did you stay in hospital because of a physical health problem*?’

Finally, to measure criminal justice system contact, participants reported whether they had been in contact with the following channels of the justice system over the past 12 months (yes/no): held in an adult prison; held overnight by police; attended court for a criminal matter; under supervision of a Parole or other Justice Officer; or stopped by police on the street. From this, the total number of different criminal justice system channels participants had been in contact with over the past 12 months was computed (range 0–5). Participants also reported the number of days over the past 12 months they had contact with each criminal justice system channel (range 0–365 days).

#### Semi-structured interviews with clients and stakeholders

The qualitative component comprised semi-structured interviews to explore the key elements and processes of the service delivery of each model. The design of the client interviews was intended to reflect the different housing arrangements; one-on-one interviews were conducted with Platform 70 clients as they lived independently, whereas group interviews were conducted with Common Ground clients as they resided in a congregated setting. For Platform 70 clients, case managers initially recommended clients who varied in tenancy outcomes (sustained or failed tenancies) to take part in the interviews. All recommended clients were contacted either via the phone or by letter and invited to participate in a qualitative interview about Platform 70. In total, eight clients completed interviews during the evaluation period. Recruitment for the Common Ground client interviews was facilitated by staff who approached formerly homeless residents and informed them of the details of the group interviews. In total, 19 clients participated in a group interview. Participants received an AUD$40 food voucher as reimbursement for their travel and time.

The qualitative interviews with clients comprised a number of open-ended questions to explore their experiences and perceptions of their housing and support services. Topics covered included the circumstances that led to homelessness, the importance of having a home, perceptions of and experiences with housing providers, services and support offered and received, relationships with support services, changes in life since being housed, difficulties encountered, and future goals and aspirations.

A purposive sampling method was used for the stakeholder interviews for both housing programs, which involved targeting stakeholders with experience and knowledge regarding the implementation and operation of the programs. Stakeholder interviews were conducted with community housing providers, front-line and managerial support service representatives, and government and non-government agency staff who were equipped to provide feedback. In total, eight Platform 70 stakeholders and 30 Common Ground stakeholders completed interviews during the evaluation period. Some stakeholders were interviewed at both baseline and follow-up due to their close involvement in the programs and ability to comment on change during the evaluation timeframe (Platform 70: n = 1; Common Ground: n = 12).

Qualitative interviews with stakeholders addressed the facilitators and barriers related to achieving program objectives. Open-ended questions explored the implementation and outcomes of the housing and support, as well as the effectiveness of contractual and partnership structures embedded in the programs. Stakeholders were asked questions relevant to their experience about the process of providing housing, the development and maintenance of support, tenancy management, clients’ needs and independence, and measures of progress and success in the programs.

Clients and stakeholders who agreed to participate in the semi-structured interviews were asked to read and sign a Participant Information Statement and Consent Form. This form requested consent for the research team to audio-record and transcribe the interview for analysis. To protect participants’ privacy, neither the personal identity nor organisational affiliations will be identified in any publications.

#### Housing and support program data

Program data was accessed for the cost analysis. Of all consenting participants, a breakdown per month of their rental arrears, the arrears escalation pathway undertaken by staff, and tenancy damages were extracted. De-identified program data of all clients was also obtained, which included the duration and intensity of support services received (housing case management and health services) and tenancy stability indicators such as the total number of days housed, frequency of housing transitions since first being housed by the program, and number of neighbour complaints during the evaluation timeframe. Agencies providing support and tenancy management to clients as well as community housing providers were interviewed to ascertain the costs of program provision.

### Data analysis

Given the nature of the housing programs under evaluation, we were limited by the number of clients engaged with each program and therefore did not perform a formal power-based sample size calculation. Instead, we invited all eligible Platform 70 and Common Ground clients to participate in the client survey, and recruitment continued until all eligible clients had either provided consent or declined participation in the research.

Loss to follow-up comparisons that assesses the characteristics of participants in the two programs who completed both baseline and follow-up client surveys (completers) against those who only completed the baseline survey (non-completers) will be made. The purpose of these comparisons is to determine whether there are any key differences between survey completers and non-completers of each program. Other patterns of missing data will be examined to determine if there are potential biases. Appropriate literature that addresses how to deal with missing data and small populations and/or small samples will also be consulted.

To address Aims 1 and 2, a profile of clients engaged with the two housing programs will be constructed, which will include demographics, homelessness history and health status. Multivariate analysis will be undertaken to determine changes over time (baseline to follow-up) in key outcomes, including housing, health status and treatment rates, quality of life, substance use patterns, and contact with the health and criminal justice systems within and across the two programs. Additionally, multivariable logistic regression will be used to identify factors associated with sustained tenancies using SAS version 9.4 software.

Qualitative interviews with clients and stakeholders will be thematically analysed in line with the general inductive approach using NVivo 10 software. The analysis will identify key themes in sustained and failed tenancies. These data will be presented in such a way as to give some indication of the commonality or otherwise of particular views, but will not purport to be representative.

To address Aim 3, the cost to government of mainstream health and criminal justice service use by Platform 70 and Common Ground clients and how this use changed over time will be examined. It will also review the cost of delivering the programs and the extent to which this is offset by a decrease in the cost of mainstream government services use by participants.

A detailed examination of mainstream services will utilise the health and criminal justice system contact data collected in the client surveys. Associated costs incurred in the 12 months prior to the baseline client survey will be compared with the cost of services used in the 12 months prior to the follow-up client survey. The cost of health and justice services will also be compared with the NSW population average.

The cost of health and justice services used by client survey participants will be estimated by applying the unit cost for each service to reported use. Unit costs will be estimated from publicly available information including the Report on Government Services 2013 [42] and various other reports, including those published by the Australian Institute of Health and Welfare [43-47]. These sources will also be used to estimate average service use and associated cost for the NSW population.

The cost of delivering the Platform 70 and Common Ground programs will be examined with reference to recurrent expenditure for the period in which clients were housed in the program. We shall also consider the range of rental subsidies provided to clients in the two housing models. Funding and expenditure data will be sought directly from the providers of social, health and tenancy management, and administrative services. To estimate the recurrent cost incurred by housing providers to manage and maintain properties, we shall draw on estimates obtained from the Report on Government Services [42]. Platform 70 and Common Ground case workers potentially provide more time to resolving issues associated with their tenancies than is normal. This implies that the average recurrent cost/dwelling is likely to represent a conservative estimate of the cost incurred by housing providers.

Housing providers also incur the capital cost of accommodation. In our cost analysis we will only consider public and community housing capital costs in the Common Ground program as Platform 70 involves the head leasing of privately owned dwellings. The average capital value of public housing and community housing properties available to Common Ground clients will be established and the annualised value of capital employed estimated by applying an opportunity cost of capital of 8% [42] to the average capital value.

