### Aims

While the Housing First approach has been evaluated internationally [27,20,28,29] and is being keenly applied in Australia, there has been a paucity of evidence on the effectiveness of Australian adaptations of the approach. Findings from evaluations of individual Housing First programs within Australia have recently been released publicly [30,31], however no study examining more than one of these adaptations with the same methodology has been conducted. Further, evaluations to date have focused largely on housing sustainability rather that incorporating broader measures of health and quality of life. Given this, there remains a pressing need to determine the efficacy of these respective models (Platform 70 [scatter site]; Common Ground [congregated site]) in relation to both housing and health outcomes. In response to this gap in the evidence-base, we have commenced a longitudinal analysis of these two adaptations using a standardised mixed methods approach to examine the changes in housing and health outcomes associated with the respective models.

Specifically, we aim to:Determine whether changes occurred with respect to clients’ housing stability, physical and mental health and treatment rates, psychological distress, quality of life, substance use patterns, and health and criminal justice system contact.Identify the demographic and social characteristics of clients that predicted success in each model. For the purposes of this study, success was defined as sustained tenancy and improved health and well-being outcomes.Calculate the net of ‘cost offsets’ of the two programs; that is, the reduction in measurable health, criminal justice and other costs borne by government as a consequence of the program.

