For the 12-month follow-up survey, the participant retention rate was 79% (Platform 70: 37 of 45 participants, 82%; Common Ground: 26 of 35 participants, 74%), which is comparable with longitudinal studies of Housing First programs internationally [29,35]. Follow-up surveys were conducted from October 2013 to May 2014. Nine baseline Platform 70 participants did not complete the follow-up survey due to not being contactable (n = 6), refused (n = 2) or incarcerated (n = 1). Similarly, nine baseline Common Ground participants did not complete the follow-up survey due to not being contactable (n = 6), refused (n = 1), incoherent (n = 1) or passed away (n = 1).

The following measures were collected at both baseline and 12-month follow-up surveys, with the exception of some demographic variables that would not change over time (e.g., sex). To maximise the sample sizes, all eligible Platform 70 and Common Ground clients were invited to participate in the client survey, and recruitment continued until all eligible clients had either provided consent or a reason for non-participation in the research had been ascertained.

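### Aim 2 defines success as sustained tenancy plus improved health and well-being, but the only stated predictor model has tenancy as its outcome, and the sample caps what that model can carry in each program

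*Protocol article*

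**What the plan says.** The Aims section sets the second aim as: "Identify the demographic and social characteristics of clients that predicted success in each model". It then fixes the meaning of the target: "success was defined as sustained tenancy and improved health and well-being outcomes".

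The Data analysis section has one paragraph for Aims 1 and 2 together. It offers three things:

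- a descriptive profile of clients;
- an analysis of change: "Multivariate analysis will be undertaken to determine changes over time (baseline to follow-up) in key outcomes", covering housing, health, quality of life, substance use and service contact, within and across the two programs;
- a predictor model, to be run in SAS 9.4: "multivariable logistic regression will be used to identify factors associated with sustained tenancies".

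The section names no estimator and no predictor list, and does not say whether the regression is fitted in each program or pooled. On small numbers it says: "Appropriate literature that addresses how to deal with missing data and small populations and/or small samples will also be consulted". The limitations text adds that effort went into finding suitable small-sample techniques, without naming one.

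On tenancy outcomes, the section on housing and support program data says: "De-identified program data of all clients was also obtained". These records include days housed and housing transitions.

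**The concern.** The outcome in the aim and the outcome in the model differ. The aim has a two-part outcome, while the model has the first part only. The article criticises earlier evaluations for concentrating on housing sustainability, so a predictor analysis limited to tenancy would repeat the gap that the study sets out to fill. A reader of the results could take predictors of keeping a tenancy for predictors of success as the article defines it.

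The second issue is how much the tenancy model can carry. Aim 2 asks for predictors in each model. If that means a separate multivariable fit in each program, the numbers are very small. Odds ratios from such fits can be infinite or badly biased away from 1, and a list of apparent predictors could reflect chance.

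**Working it through.** **Part 1: aim against analysis.**

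| Element of Aim 2 | Analysis stated for it |
|---|---|
| Predictors of sustained tenancy | Multivariable logistic regression |
| Predictors of improved health and well-being | None stated; the multivariate analysis estimates change from baseline to follow-up |
| In each housing model | Change is to be examined within and across programs; for the logistic regression, nothing is said |

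An analysis of mean change shows whether a program's clients improved on average. It does not show which characteristics go with improvement unless those characteristics enter as predictors of the follow-up score, and the text does not say that they do. No composite success variable and no threshold for improvement is given.

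**Part 2: the cap on events.**

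Inputs from the Client surveys section:

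- Baseline participants: 45 (Platform 70) and 35 (Common Ground), 80 in total.
- Follow-up: "Platform 70: 37 of 45 participants, 82%; Common Ground: 26 of 35 participants, 74" per cent.

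The stated retention reproduces: 37/45 = 82.2%, 26/35 = 74.3%, and (37 + 26)/80 = 63/80 = 78.8%, given as 79%.

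Input from the Demographics section: eight variables (sex, age, Indigenous status, Grade 10, relationship, number of children, employment, cognitive impairment). Homelessness history and health would come on top.

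Formula: in a sample of n with a yes/no outcome, the rarer outcome is at most n/2, rounded down. Events per predictor is at most that number divided by 8. This needs no assumed failure rate.

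| Sample | Largest possible rarer outcome | Divided by 8 |
|---|---|---|
| Platform 70 completers, n = 37 | 18 | 2.3 |
| Common Ground completers, n = 26 | 13 | 1.6 |
| Platform 70 baseline, n = 45 | 22 | 2.8 |
| Common Ground baseline, n = 35 | 17 | 2.1 |

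The article lists nine Platform 70 losses (6 + 2 + 1), whereas 45 − 37 = 8. If nine is right, n is 36 and the cap is still 18.

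**Part 3: illustration under assumed failure rates.** The article gives no count or rate of failed tenancies. The table shows expected failures among completers, n × rate:

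| Assumed failure rate | Platform 70 (n = 37) | Common Ground (n = 26) |
|---|---|---|
| 10% | 3.7 | 2.6 |
| 20% | 7.4 | 5.2 |
| 30% | 11.1 | 7.8 |
| 50% | 18.5 | 13.0 |

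A simulation of unpenalised maximum likelihood with eight predictors (500 datasets per cell, assumed predictor distributions, a true odds ratio of 2 for one predictor) gave separation or non-convergence in 73% of datasets at n = 37 and 92% at n = 26 with 20% failures. With 50% failures, the most favourable split, the figures were 36% and 65%. These percentages depend on the assumed failure rate, predictors and estimator. They show what could happen and are not properties of the stated plan.

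**The case against.** The best defence has three parts.

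*The paragraph covers Aims 1 and 2 jointly.* The multivariate analysis of health and quality of life therefore sits under both aims, and covariates could be specified in a fuller plan. This shows that the gap may be closed elsewhere. It does not remove the mismatch, because the article fixes the outcome of the predictor model as tenancy and the purpose of the other analysis as change over time.

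*Estimator, predictor list and pooling are details that an article may leave to its analysis plan.* This stands, and their absence is not counted here as an error. A reader might infer that unpenalised maximum likelihood fitted separately in each program is the plan. The article does not say so, and it twice signals an intention to use small-sample methods. Nor can a reader say as fact that failures are too few, since no count is given. What remains is the cap, which any later plan has to respect.

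*Tenancy indicators exist beyond the survey completers.* This also stands, and is why the cap is given for the baseline sample too. It eases the limit only slightly (2.8 and 2.1 against 2.3 and 1.6). A reader might go further and propose a predictor model on all 122 clients (70 + 52). The listed de-identified records name no individual demographics and Table 1 gives only aggregate figures, so the documents do not show that such a model is possible.

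A further tempting inference is that survey entry more than a year after opening selects tenants who had survived the early period, so that sustainment is overstated. The documents do not support this. Eligibility includes people waiting for housing, a client rehoused after a failed tenancy can remain eligible, and neither entry dates nor counts of early leavers are given.

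**Conclusion.** The mismatch between Aim 2 and its analysis holds on the text alone and rests on no assumption: the stated predictor analysis covers one of the two parts of success. The plan should be changed before the Aim 2 results are presented as predictors of success.

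The sample-size part holds as an upper limit. A program-specific model with the eight listed demographics has at most about 2.3 and 1.6 events per predictor among completers, or 2.8 and 2.1 if tenancy outcomes are available for every baseline participant. This assumes one model term per demographic variable. It further assumes fitting in each program, which is inferred from the wording of Aim 2 and not stated in the Data analysis section. The actual number of failed tenancies, and so any rate of separation, is unknown from the documents.

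**What to change.** 1. Add predictor models for the health and well-being part of success: the follow-up Global Severity Index and each WHOQOL-BREF domain as outcomes, adjusted for the baseline score, on the same client characteristics as the tenancy model. These use data already collected from survey completers.
2. Fit the tenancy model with Firth-penalised logistic regression, available in the stated SAS 9.4, and a short predictor list chosen before the outcomes are examined. For scale, three predictors would give at most 18/3 = 6 and 13/3 = 4.3 events per predictor among completers, so penalisation is still needed.
3. Take tenancy outcomes for all baseline participants from program data where linkage to the survey allows, and say so if it does not.
4. State whether the fit is pooled or by program. If pooled with a program term, say that the model estimates effects common to both programs, and that program-specific predictors, which Aim 2 asks for, are exploratory.

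The cost is analysis wording, a few more models, and fewer predictors in each. Pooling also gives up firm answers on predictors specific to each housing model. The alternative to step 1 is to narrow the definition of success in Aim 2 to sustained tenancy, which would be consistent but would drop the health question that the article presents as its contribution.

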### Participants, setting and measures

#### Client surveys

Eligibility criteria to participate in the client surveys were that participants had to be at least 18 years old at baseline, were able to provide informed consent, had a history of chronic homelessness (more than six months history of sleeping rough), and were currently housed or waiting for housing with the Platform 70 or Common Ground programs. All individuals housed through these two programs had to firstly be engaged through the Way2Home assertive outreach program, and as such would have received support prior to entering either housing program.

Initially, all eligible clients were asked by their case manager whether they would consent to being approached by a trained researcher to explain the details of the study. All clients who agreed to participate were provided with a Participant Information Statement and Consent Form which they were asked to read and sign. If a participant was unable to read, all information and instructions were read aloud. The survey was then administered by a trained researcher who read the questions to the participant and recorded their responses in a pen and paper format. Upon completion, the survey was sealed in an envelope and returned to the research supervisor for a quality control check (see Additional file 2 for further information on recruitment process).

Surveys were conducted in a neutral public space that was convenient and comfortable for the participant, such as a park, café or an available consultation room at Common Ground. As compensation for their time and travel, participants were offered an AUD$40 food voucher [33]. All researchers completed a three-hour training session on administering the client survey and adhering to an interviewer safety protocol [34]. On average, surveys took 45 minutes to complete.

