To reduce loss at follow-up, a systematic process for locating and communicating with participants for the follow-up survey was implemented (see Additional file 3). With their consent, at baseline participants filled out a Locator Form asking them for their primary contact information (e.g., phone number, mailing address, email address) and the contact information for family, friends or service providers with whom they have regular contact. The form provided space for participants to note down any specific instructions for contacting them or their nominated contacts. Participants were also asked to sign a Release of Information Form, which provided consent for the researchers to obtain their contact details from Centrelink (a government agency responsible for welfare payments) if other methods of follow-up were not successful. This form provided space for participants to record their Centrelink client identification number to facilitate record access and matching. Signing the Locator and Release of Information forms were voluntary and a decision not to sign either form did not exclude participants from being involved in the research.

In total, 80 participants were recruited at baseline, which equated to a recruitment rate of 66% (Platform 70: 45 of 70 clients recruited, 64%; Common Ground: 35 of 52 clients recruited, 67%). Reasons for non-recruitment included refusal, unable to make contact, non-English speaking, incarcerated and away during the recruitment timeframe. Baseline data collection occurred from November 2012 to May 2013. As shown in Table 1, the demographic compositions of the two samples are mostly similar to that of all clients within the programs.

**Table 1 Tab1:** **Demographic composition of the client survey samples recruited at baseline compared to the overall populations**

**Demographics**	**Platform 70 (scatter site)**		**Common Ground (congregated site)**	
	**Sample (n = 45)**	**Population (N = 70)**	**Sample (n = 35)**	**Population (N = 52)**
Sex (% male)	84	83	77	77
Mean age (years)	44	43	44	44
% Indigenous	20	28	10	14
% born in Australia	82	86	73	74

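### The NSW cost benchmark is named without age or sex standardisation, although the clients are all adults and about 81% male

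*Protocol article*

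**What the plan says.** The protocol article's Data analysis section sets out two cost comparisons for mainstream services.

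- **Before and after, in the same clients:** "Associated costs incurred in the 12 months prior to the baseline client survey will be compared with the cost of services used in the 12" (the quote stops here; the second period is the year up to the follow-up survey).
- **Against the state:** "The cost of health and justice services will also be compared with the NSW population average". The benchmark comes from the published reports that also supply the unit costs: "These sources will also be used to estimate average service use and associated cost for the NSW population".

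No age range, sex split or standardisation is given for the state figure. On the client side, the Client surveys section requires that "participants had to be at least 18 years old at baseline". Table 1, in the same section, reports the percentage male for the Platform 70 sample and population and then the Common Ground sample and population: "Sex (% male) 84 83 77 77". Mean age is 43 or 44 in all four columns.

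Aim 3 is defined in the Aims section as the net cost offset, that is, "the reduction in measurable health, criminal justice and other costs borne by government as a consequence of the program".

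**The concern.** An average over a whole state population includes children and is roughly half female. The clients are adults, and about four in five are men. Contact with the justice system would be expected to vary strongly with age and sex. One of the channels measured, adult prison, can hardly apply to children at all. Health service use also varies with age and sex, though not in one direction across services. A group of adults, mostly men, would therefore be expected to differ from the state average even without any history of homelessness.

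The study has no control group, so in the cost analysis this is the only comparison with people outside the two programs. A policy reader may well take the gap as what this client group costs government beyond otherwise similar people. An unstandardised figure does not show that.

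**Working it through.** **Is there a figure to reproduce?** No. The article states no NSW cost, client cost or expected difference, and no error rate or power enters the point (the authors "did not perform a formal power-based sample size calculation").

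**Sex mix of the clients.** The inputs are the Table 1 percentages and the recruitment counts ("Platform 70: 45 of 70 clients recruited, 64%; Common Ground: 35 of 52 clients recruited, 67" per cent).

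- Sample: (0.84 × 45 + 0.77 × 35) / 80 = (37.80 + 26.95) / 80 = 80.9% male. In whole people, 84% of 45 is 38 and 77% of 35 is 27, so 65 of 80.
- All clients: (0.83 × 70 + 0.77 × 52) / 122 = (58.10 + 40.04) / 122 = 80.4% male.

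**Justice costs.** Let *p* be the share of men among clients, *r* the male:female ratio of adult justice cost, and *c* the share of the population who are children, taken to have no justice cost. Take the state population as half male. The expected cost of adults with the clients' sex mix, relative to the all-ages average, is

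[*p r* + (1 − *p*)] / [((1 + *r*) / 2) × (1 − *c*)].

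Only *p* comes from the article. The values of *r* (2 to 10), *c* (0 to 0.25), the half-male population and the zero cost for children are assumptions.

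| *r* | *c* | Platform 70 (*p* = 0.84) | Common Ground (*p* = 0.77) |
|---|---|---|---|
| 2 | 0 | 1.84 / 1.5 = 1.23 | 1.77 / 1.5 = 1.18 |
| 2 | 0.25 | 1.84 / 1.125 = 1.64 | 1.77 / 1.125 = 1.57 |
| 10 | 0 | 8.56 / 5.5 = 1.56 | 7.93 / 5.5 = 1.44 |
| 10 | 0.25 | 8.56 / 4.125 = 2.08 | 7.93 / 4.125 = 1.92 |

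The range is therefore 1.23 to 2.08 for Platform 70 and 1.18 to 1.92 for Common Ground. The formula treats all adults alike with respect to age, so it says nothing about the effect of older people in the state average.

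**Between programs.** The two factors differ by 1.84 / 1.77 = 1.04 at *r* = 2 and by 8.56 / 7.93 = 1.08 at *r* = 10, that is, by about 4 to 8%.

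**Health costs.** Here women may cost more than men, and children do have costs. Let *k* be the child:adult cost ratio, so that (1 − *c*) becomes (1 − *c*) + *c k*, and take *p* = 0.81.

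- *r* = 0.8, no child effect (*k* = 1): (0.81 × 0.8 + 0.19) / 0.9 = 0.838 / 0.9 = 0.93.
- *r* = 0.8, *c* = 0.25, *k* = 0.5: 0.931 / 0.875 = 1.06.

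The factor falls on either side of 1, depending on inputs that the documents do not give.

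**The case against.** **The article does not say the average is crude or covers all ages.** This is true. It is the ordinary reading of a population average with no qualifier, but it is an inference. A condensed article may leave the reference population to the full plan, and an adult or standardised figure is not ruled out. What remains is that the comparator itself is named, and that following the text as written gives a benchmark that does not match the clients. If the full plan already uses a matched figure, one phrase settles the matter.

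**No causal claim rests on the benchmark.** This is also true. A reader might infer that the plan reports an excess cost and attributes it to homelessness, but the article does neither. Cost per client beside cost per resident is a legitimate description of government spending. The point is therefore about how the figure will be understood and about a more useful comparator. It does not show a biased estimate of a declared effect.

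**The size is assumed.** This stands. Twofold is the extreme corner (ratio 10, a quarter of the population children); the low end is 1.2, and the calculation for that range covers justice costs only.

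**The programs barely differ.** This stands too. The factors differ by 4 to 8%, the sex difference amounts to two or three people, and no comparison of the programs through the NSW average is planned.

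**Conclusion.** The point holds in a limited form. The named benchmark is a general-population average, the clients are adults and about 81% male, and no adjustment for either is described. Part of any gap from that average would then reflect age and sex. For justice costs the expected ratio from these alone is about 1.2 to 2.1 under the stated assumptions; for health costs the direction is uncertain. The documents contain no NSW rates from which a corrected figure could be computed.

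It would be wrong to conclude that Aim 3 is compromised. Its cost offset compares clients' own costs before baseline and before follow-up, and sets program costs against any decrease. None of that uses the NSW average, which enters as an additional benchmark. The issue is secondary, but it concerns a policy-facing figure and is cheap to put right.

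**What to change.** Define the benchmark as an expected cost: apply NSW adult age- and sex-specific service-use rates to each program's age-sex distribution, then multiply by the same unit costs used for the clients. Where a source gives no strata, use the adult rate if available and label that comparison descriptive and unadjusted.

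Age and sex are already collected in the client survey, so no new client data are needed. The cost is some desk work with published tables and a sentence or two in the analysis plan. Whether the cited reports give stratified rates for every service cannot be checked from the documents, so some services may remain unadjusted; the label covers those.
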